## Methods

### Study objective

The key objectives of NINCFB are as follows:Determine the long-term efficacy of NAC in improving QoL of patients with NCFB.Determine the long-term effecacy of NAC in reducing exacerbation frequency of patients with NCFB.Explore the activities of NAC in antibiosis, anti-inflammation and antioxidation for the treatment of NCFB.Evaluate the long-term influence of NAC on clinical manifestations, pulmonary function and computed tomographic imaging features of patients with NCFB.Evaluate the long-term adverse effects of NAC on patients with NCFBConducting a subgroup analysis to investigate the different effectiveness of NAC on NCFB with different severities and causes, such as pathogen infection, immune deficiency and congenital defects.Trace biomarkers that can be predictors of NCFB progression or indicators of NAC efficacy.

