#### Secondary endpoints

The main secondary endpoint is 16S rRNA assessed in microbial testing of sputum, which is a measurement of airway bacterial colonization in NCFB. The levels of inflammatory factors, including interleukin-1-beta (IL-1β) [26], interleukin-8 (IL-8) [27], tumour necrosis factor-alpha (TNF-α) [28] and matrix metalloproteinase-9 (MMP-9) [29], and the levels of oxidative stressors, such as myeloperoxidase (MPO) [30], total antioxidant capacity (TAC) [31], superoxide dismutase (SOD) [32] and malondialdehyde (MDA) [20], in sputum and serum will also be detected through enzyme-linked immunosorbent assays (ELISAs) (Table 2).

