### Statistical analysis

The resulting data will then be analysed with SPSS V.26 by statistical experts. Primary outcomes of each group will be compared by Student’s t test (t test) or the Wilcoxon rank-sum test after calculating its normal distribution and will be expressed in terms of the mean, standard deviation (SD) or median to indicate the long-term efficacy of NAC for NCFB. The comparison between the NAC group and the control group in terms of 16S rRNA and the levels of inflammatory factors and oxidative stressors will be of vital importance. In addition, NINCFB will also use the t-test, chi-square test and Wilcoxon rank-sum test to evaluate baseline discrepancy and other variables. Regression analysis and the correlation coefficient may confirm the predictors of disease progression and indicators of NAC efficacy.

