### Subgroup analysis

This trial will perform subgroup analysis by differentiating the participants according to 1) BSI scores (mild: 0–4 points, moderate: 5–8 points, severe: ≥ 9 points); 2), airway bacterial colonization (*Pseudomonas aeruginosa*, *Staphylococcus aureus*, and others); 3), number of lesion lung lobes (lesion lung lobes < 3 or ≥ 3); 4) FEV_1_/FVC (FEV_1_/FVC ≥ 70% or < 70%); 5) number of exacerbations in the 12 months prior to the start of the study (exacerbations frequency: ≤ 2 times per year, and > 2 times per year).

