### Sample size

We calculate the sample size required for the evaluation of primary outcome-1 (SGRQ scores) and primary outcome-2 (number of exacerbations) respectively. As NAC is effective in reducing sputum of patients with NCFB in clinical practice, we design a ratio of 2:1 for the sample size of intervention group to control group in this study so that two-thirds of enrolled patients could receive effective treatments. For the SGRQ score, we regard mean difference (MD) of 6 points of SGRQ score as the smallest clinically important difference between two group with a standard deviation (SD) of 8.5 used in the calculation, according to the previous report of NAC on patients with COPD [35–37]. Based on 90% power with a two-sided significance level of 5%, a sample size of 64 for intervention group and 32 for control group is needed as calculated by the software PASS 15. In addition, assuming 20% of patients in each group may drop out or lose data integrity, we need to recruit 79 in the intervention group and 40 in the control group. For the number of exacerbation, we regard MD of 0.7 times of exacerbation per year as the smallest clinically important difference between two group with a SD of 1 used in calculation, according to the published study of NAC on patients with postinfection or idiopathic bronchiectasis [21]. Considering 20% dropout, we also need to recruit 79 patients in NAC group and 40 patients in placebo group (α = 0.05, 1 - β = 0.9). Taken together, this study eventually aims to enroll 119 participants, of them, 79 in the NAC group and 40 in the placebo group.

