### Bias control

The inclusion and exclusion criteria of this study are clearly designed to reduce selection bias. Detailed data collection and strict quality management procedures will be formulated. All procedures are in accordance with the unified standard operating procedure (SOP), and trial-related tests will be conducted by experts at West China Hospital of Sichuan University to ensure the consistency of the results and reduce information bias. The final outcomes will be analysed by comprehensive statistical methods such as standardization, multivariate analysis, and propensity scoring to control for confounding factors.

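### Correlation is named among the methods that may confirm indicators of NAC efficacy, but a marker–outcome correlation cannot separate a prognostic marker from one tied to the drug's effect

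*Protocol article*

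**What the plan says.** The last objective listed in the protocol article's Study objective section is: "Trace biomarkers that can be predictors of NCFB progression or indicators of NAC efficacy". It joins two questions, one about the course of the disease and one about the drug. The Statistical analysis section answers both in one sentence: "Regression analysis and the correlation coefficient may confirm the predictors of disease progression and indicators of NAC efficacy". No outcome, marker, model term or analysis population is attached to it.

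Three other places bear on the point:

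- Statistical analysis also plans, as a separate item, "The comparison between the NAC group and the control group in terms of 16S rRNA and the levels of inflammatory factors and oxidative stressors". Table 2 schedules these measurements at baseline, 26 weeks and 52 weeks.
- Subgroup analysis lists five factors, beginning "This trial will perform subgroup analysis by differentiating the participants according to 1) BSI scores". None is an inflammatory or oxidative marker, and no interaction test is stated.
- Bias control mentions "standardization, multivariate analysis, and propensity scoring to control for confounding factors". The stated purpose is confounding, not variation in the treatment effect.

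**The concern.** The two halves of the objective have different null hypotheses. For a predictor of progression, the null is that marker and outcome are unrelated, and a correlation or simple regression tests that. For a baseline marker that indicates who benefits from NAC, the null is that the NAC–control difference is the same at every marker level. A marker related to outcome equally in both arms violates the first null and satisfies the second. If its correlation with outcome is taken as evidence about NAC, an ordinary severity marker can be reported as an efficacy marker even when NAC does nothing.

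At stake is the biomarker objective. The article presents the trial as evidence for guideline revision and as a way to find differences in NAC efficacy across a heterogeneous disease, so a mislabelled marker would matter to readers.

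**Working it through.** **Inputs from the protocol article, Sample size.** For SGRQ, "we regard mean difference (MD) of 6 points of SGRQ score as the smallest clinically important difference", "with a standard deviation (SD) of 8.5 used in the calculation"; 90% power; two-sided 5%; 2:1 allocation; 20% dropout; 64 and 32 evaluable. **Assumption.** The correlation r between marker and outcome is not given, so it is varied from 0 to 0.5.

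**1. The plan's own figure.** Control n = (1.96 + 1.2816)² × 8.5² × (1 + 1/2) / 6² = 10.51 × 72.25 × 1.5 / 36 ≈ 31.6, so 32 control and 64 NAC. The unrounded values divided by 0.8 give about 40 and 79. The stated sample size reproduces, and 64 + 32 = 96 is the right base for what follows.

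**2. A purely prognostic marker.** Simulation, 20,000 trials per case. The marker is standard normal. The outcome is 8.5 × (r × marker + √(1 − r²) × error), minus a constant NAC effect of 0 or 6 points. The marker–outcome link is the same in both arms, so the true arm-by-marker interaction is zero. Share of trials with two-sided p < 0.05:

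| r | Pooled correlation, no NAC effect | Pooled correlation, 6-point NAC effect | Correlation in NAC arm only | Arm-by-marker interaction |
|---|---|---|---|---|
| 0 | 5% | 5% | 5% | 5% |
| 0.2 | 50% | 46% | 35% | 5% |
| 0.3 | 85% | 81% | 68–69% | 5% |
| 0.4 | 98% | 97% | 92% | 5% |
| 0.5 | 99.9% or more | 99.9% | 99% | 5% |

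**3. Hand check of one row.** By Fisher's z at r = 0.3 and n = 96: atanh(0.3) × √93 = 0.3095 × 9.644 = 2.985, and Φ(2.985 − 1.96) ≈ 0.85. In the NAC arm with n = 64: 0.3095 × √61 = 2.417, and Φ(2.417 − 1.96) ≈ 0.68. Both agree with the simulation.

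**4. What the interaction test can detect.** For a marker split at its median, the standard error of the difference in NAC effect between halves is 2 × 8.5 × √(1/64 + 1/32) = 3.68. For a true 6-point difference, 6 / 3.68 = 1.63, and power is Φ(1.63 − 1.96) ≈ 0.37.

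The simulation covers a baseline marker and a continuous SGRQ-type outcome. It does not model exacerbation counts or markers that change on treatment.

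**The case against.** The best defence is that the sentence names regression first, and the regression needed here (outcome on arm, marker and their product) falls within it. Model terms are ordinary analysis-plan content, and no such plan is shown. The wording says only that the methods may confirm, with no threshold or decision rule. *Indicator of NAC efficacy* is undefined and could mean a marker that moves on treatment. A baseline interaction is not the test for that reading, and a NAC–control comparison of marker levels is already planned.

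Much of this stands, and it rules out stronger readings that a reader might infer:

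- *That the plan relies on correlation alone.* It does not, since regression is named beside it.
- *That the placebo arm goes unused for markers.* The planned between-arm comparison contradicts this.
- *That a severity marker would be declared an efficacy marker.* Without a decision rule, the text supports only that it could be. The rate depends on r and is 5% at zero.
- *That the lack of error control over the named markers is a fault.* Multiplicity over exploratory markers is commonly left to the analysis plan.

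What does not stand is the defence of correlation itself. It is named as a tool for the efficacy claim, and under no reading of *indicator* can it do that work. Between-arm comparison of levels shows whether NAC moves a marker, but the article does not connect it to the indicators claim. A later plan could add a model, yet this sentence would still assign correlation a question that it cannot answer.

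**Conclusion.** The point holds as a stated method that does not fit half of its objective. Under the assumed r of 0.2 to 0.4, with 64 and 32 evaluable, a marker with no bearing on NAC's effect passes a pooled correlation test in about 50% to 98% of trials, or about 46% to 97% if NAC has a constant 6-point effect. The interaction test passes it in about 5%. The contrast holds at every non-zero r examined. The absolute rates rest on r, which the document does not give, and on the baseline-marker reading of *indicator*.

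The correction is worth making because the sentence governs a listed objective. The primary comparisons of SGRQ and exacerbations, the sample size and the between-arm comparisons of the secondary endpoints are untouched.

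**What to change.** Split the sentence in Statistical analysis and define *indicator of NAC efficacy*:

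1. **Predictors of progression:** regression of the 52-week outcome on the baseline marker, adjusted for arm.
2. **Baseline markers of NAC efficacy:** one regression in both arms on arm, baseline marker and arm-by-marker interaction, with any claim resting on the interaction.
3. **On-treatment response markers:** any claim rests on the NAC–control difference in the marker's change. This shows that NAC moves the marker, not by itself that the marker reflects clinical benefit.
4. **Correlation:** for description or prognosis only.
5. **Wording:** replace *confirm* with *explore*.

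The cost is wording and one model term, with no new data or patients. The downside is low power: about 37% for a 6-point difference in effect between the halves of a median-split marker. Fewer markers will be claimed, a non-significant interaction will not show that the NAC effect is uniform, and findings should be reported as hypothesis-generating.

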### Subgroup analysis

This trial will perform subgroup analysis by differentiating the participants according to 1) BSI scores (mild: 0–4 points, moderate: 5–8 points, severe: ≥ 9 points); 2), airway bacterial colonization (*Pseudomonas aeruginosa*, *Staphylococcus aureus*, and others); 3), number of lesion lung lobes (lesion lung lobes < 3 or ≥ 3); 4) FEV_1_/FVC (FEV_1_/FVC ≥ 70% or < 70%); 5) number of exacerbations in the 12 months prior to the start of the study (exacerbations frequency: ≤ 2 times per year, and > 2 times per year).

### Sample size

We calculate the sample size required for the evaluation of primary outcome-1 (SGRQ scores) and primary outcome-2 (number of exacerbations) respectively. As NAC is effective in reducing sputum of patients with NCFB in clinical practice, we design a ratio of 2:1 for the sample size of intervention group to control group in this study so that two-thirds of enrolled patients could receive effective treatments. For the SGRQ score, we regard mean difference (MD) of 6 points of SGRQ score as the smallest clinically important difference between two group with a standard deviation (SD) of 8.5 used in the calculation, according to the previous report of NAC on patients with COPD [35–37]. Based on 90% power with a two-sided significance level of 5%, a sample size of 64 for intervention group and 32 for control group is needed as calculated by the software PASS 15. In addition, assuming 20% of patients in each group may drop out or lose data integrity, we need to recruit 79 in the intervention group and 40 in the control group. For the number of exacerbation, we regard MD of 0.7 times of exacerbation per year as the smallest clinically important difference between two group with a SD of 1 used in calculation, according to the published study of NAC on patients with postinfection or idiopathic bronchiectasis [21]. Considering 20% dropout, we also need to recruit 79 patients in NAC group and 40 patients in placebo group (α = 0.05, 1 - β = 0.9). Taken together, this study eventually aims to enroll 119 participants, of them, 79 in the NAC group and 40 in the placebo group.

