#### Primary endpoints

The primary endpoints of the NINCFB are quality of life (St George’s Respiratory Questionnaire, SGRQ scores) and the number of exacerbations during the follow-up period. The SGRQ, a comprehensive questionnaire to estimate pulmonary symptoms and living conditions, is commonly used to assess a patient’s quality of life [22, 23] and has good psychometric properties for the NCFB [24]. Exacerbation of NCFB is defined by the British Thoracic Society as acute deterioration (usually over several days) with worsening local symptoms (cough, increased sputum volume or change in viscosity, increased sputum purulence with or without increasing wheezing, breathlessness, or haemoptysis) and/or systemic upset [25]. This study has two variables designed to determine whether the long-term effectiveness of NAC achieves the treatment goal of NCFB (Table 2).

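### Two primary endpoints are each sized at the full 5% level and 90% power with no success rule, so either the familywise error is about 8–10% or the power to win both is about 80–85%

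*Protocol article*

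**What the plan says.** The Primary endpoints section gives two variables equal standing: "The primary endpoints of the NINCFB are quality of life (St George’s Respiratory Questionnaire, SGRQ scores) and the number of exacerbations during the follow-up period".

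In the Sample size section they are handled separately: "We calculate the sample size required for the evaluation of primary outcome-1 (SGRQ scores) and primary outcome-2 (number of exacerbations) respectively". For SGRQ it takes a mean difference of 6 points "with a standard deviation (SD) of 8.5 used in the calculation" and concludes: "Based on 90% power with a two-sided significance level of 5%, a sample size of 64 for intervention group and 32 for control group". With 20% dropout this becomes 79 and 40. For exacerbations it takes a difference of 0.7 per year with SD 1 and reports "we also need to recruit 79 patients in NAC group and 40 patients in placebo group (α = 0.05, 1 - β = 0.9". The two results are then merged into one enrolment target of 119, which is what each calculation gives alone.

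The Statistical analysis section compares the primary outcomes between groups by a t test or Wilcoxon rank-sum test. It names no significance level, no division of alpha, no testing order and no requirement that both succeed.

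**The concern.** With two primary endpoints, the error rate and power of the trial depend on what counts as success. If NAC may be declared effective on whichever endpoint reaches p < 0.05, there are two chances of a false positive. If both must reach it, there are two chances to fail. A sample size that gives each endpoint full alpha and 90% power makes no allowance for either.

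The practical stake is a split result, for example SGRQ significant and exacerbations not. As written, that result has no agreed meaning, and it could be interpreted after the data are seen. The abstract says the results are meant to inform treatment guidelines, so the point bears on the trial's main claim.

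**Working it through.** **Inputs (Sample size section).** SGRQ: difference 6, SD 8.5, two-sided 5%, 90% power, 64/32 evaluable. Exacerbations: difference 0.7, SD 1, alpha 0.05, 90% power. Ratio 2:1, dropout 20%. The correlation between the two test statistics is not given; I assume values from 0 to 0.8.

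**1. Reproduce the plan's figure.** Control n = (1 + 1/2) × (1.960 + 1.282)² × (SD/MD)², where (1.960 + 1.282)² ≈ 10.51.
- SGRQ: 1.5 × 10.51 × (8.5/6)² = 31.6, so 32 control and 64 NAC, as stated. Unrounded, with dropout: 63.3/0.8 = 79.1 and 31.6/0.8 = 39.5, in line with 79/40.
- Exacerbations: 1.5 × 10.51 × (1/0.7)² = 32.2 control and 64.3 NAC. With dropout: 40.2 and 80.4, about 121 against the stated 119. The gap is immaterial.

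Sidedness is written only for SGRQ. One-sided 5% for exacerbations would need only about 27 control and 54 NAC evaluable (34 and 68 with dropout), so 79/40 implies a two-sided test.

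**2. Power of each endpoint alone at 64/32.** Noncentrality = MD / (SD × √(1/64 + 1/32)), where the root is 0.2165, with 94 degrees of freedom.
- SGRQ: 0.7059/0.2165 = 3.260, giving power 89.7%.
- Exacerbations: 0.7/0.2165 = 3.233, giving power 89.3%.

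The claimed 90% for each endpoint roughly holds.

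**3. Either endpoint suffices, each tested at 0.05.** At correlation 0 the familywise error is 1 − 0.95² = 9.75%. Other values come from a bivariate normal.

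**4. Both must succeed, each tested at 0.05.** At correlation 0 joint power is 0.897 × 0.893 = 80.1%. Other values come from a bivariate normal with the step 2 powers as margins.

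| Correlation (assumed) | Familywise error, either suffices | Joint power, both required |
|---|---|---|
| 0 | 9.75% | 80.1% |
| 0.3 | 9.5% | 81.3% |
| 0.5 | 9.1% | 82.5% |
| 0.8 | 7.8% | 85.0% |

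**5. What error control costs at 64/32.**
- Alpha 0.025 for each endpoint: power 83.5% (SGRQ) and 82.9% (exacerbations).
- Holm, both assumed effects true: an endpoint succeeds if its p < 0.025, or if its p < 0.05 and the other p < 0.025. At correlation 0, SGRQ: 0.835 + (0.897 − 0.835) × 0.829 = 88.7%. Exacerbations: 0.829 + (0.893 − 0.829) × 0.835 = 88.2%. At 0.5 the values are 87.7% and 87.3%; at 0.8, 86.9% and 86.5%.
- Holm, only one endpoint has an effect: the other clears 0.025 only about 2.5% of the time, so power stays close to the 0.025 figure, about 83%.
- Fixed sequence: the first endpoint keeps full alpha and about 90% power. The second is tested only if the first succeeds, so its power to be declared is the joint figure in the table.

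**The case against.** The strongest reply is that only a journal article is at hand, and that a multiplicity rule is commonly left to the full protocol or SAP. That has force: the bare absence of a rule here would not be a finding. What remains is what the Sample size section does fix, namely full alpha for each of two primary endpoints and the single-endpoint total of 119. A later SAP could control the error at that size, but it could not raise joint power to 90% if both endpoints are required.

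A second reply is that nothing in the Sample size section is false. This also stands in part. The 90% is claimed for each endpoint separately, and it roughly reproduces.

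A third reply is that a fixed sequence would keep 5% familywise error and about 90% power for the first endpoint with the same 119 patients. That is correct, and full-alpha sizing is compatible with it. But the article states no sequence, and numbering the outcomes 1 and 2 does not set a testing order.

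A reader might infer that the trial has neither 5% error nor 90% power whichever way success is defined. The documents do not support that. Each reading breaks one property only: under an either-suffices rule the per-endpoint power stands, and under a both-required rule 5% for each test is the right level. Nor does the protocol anywhere assert 90% joint power.

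**Conclusion.** The point holds in limited form. The enrolment target of 119 is right for one primary endpoint at two-sided 5%, and the plan applies it to two without saying how they combine. The consequences are alternatives:

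- If one success is enough, the familywise error is about 9.8% at correlation 0, 9.1% at 0.5 and 7.8% at 0.8.
- If both are needed, joint power is about 80–85%.

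These figures rest on the plan's own effect sizes and SDs, on 64/32 evaluable patients, on t tests, and on the assumed correlation range. They also take 5% as the test level. That is inferred from the Sample size section, because the Statistical analysis section gives no level.

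**What to change.** State one success rule in both the Sample size and Statistical analysis sections, and give the matching power. This should be done before unblinding, which the Randomisation and double-blind section places after all participants have finished follow-up. The options at 119 patients are:

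- **Holm:** the smaller p against 0.025, then the other against 0.05. State per-endpoint power of about 87–89% if both assumed effects are true, and about 83% if only that endpoint has an effect. A plain split at 0.025 each also gives about 83%.
- **Fixed sequence:** name the order. State about 90% power for the first endpoint only.
- **Both required:** keep 0.05 for each. State joint power of about 80–85%, with the correlation assumed.

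The cost is one paragraph and a slightly less favourable stated power, with no extra patients. Extra patients arise only if the sponsor wants to keep 90%. On the t-test basis with 20% dropout, that means 78/39 evaluable and 147 enrolled (98 + 49) at alpha 0.025 each. If both are required, it means 80/40 evaluable and 150 enrolled (100 + 50) at correlation 0 to 0.3, falling to 74/37 and 140 (93 + 47) at 0.8.

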## Background

The worldwide prevalence and health care burden of non-cystic fibrosis bronchiectasis (NCFB) have been increasing rapidly in recent years [1–3]. In China, nearly 1.2% of individuals over 40 years old are diagnosed with NCFB, and its morbidity is positively correlated with age [4]. Effective therapy and management of this disease are urgently needed.

NCFB, caused by various primary pathogenic processes, such as pathogenic organism infection, immune deficiency and congenital defects [5], is a chronic purulent lung disease causing irreversible bronchial dilation and bronchial wall thickening [6, 7], which greatly complicates its treatment and management [8]. Accumulation of sputum, chronic airway inflammation and repeated exacerbations are the main characteristics of NCFB [9, 10]. Research has shown that 50% of patients with NCFB have two or more exacerbations annually, and one in three require hospitalization [11]. Continual expectoration and frequent exacerbations have significantly troubled patients and greatly reduced their quality of life (QoL) [12]. Consequently, improving airway mucus clearance, reducing exacerbation and enhancing QoL are the significant treatment goals of NCFB [13].

N-acetylcysteine (NAC), which provides the sulfhydryl group that can break the disulfide bond of the glycoprotein polypeptide chain in the phlegm to reduce the viscosity of sputum [14, 15] and can act as a direct reactive oxygen species (ROS) scavenger to regulate the redox status in the cells [16], has been recommended by treatment guidelines of chronic pulmonary disease for airway mucus clearance [15]. However, there are only a few clinical investigations on its specific efficacy for NCFB, and the long-term effectiveness of NAC for patients’ QoL has not been reported either. In addition, although NAC was determined to have antibacterial properties [17, 18] and the ability to interfere with signal pathways of inflammation [19] and oxidative stress [20] in chronic obstructive pulmonary disease (COPD), these capabilities in NCFB are still unclear [13].

A randomised controlled trial conducted by Qi, Q., et al. in 2014 demonstrated that NAC can decrease the number of exacerbations of patients with NCFB [21], but it did not evaluate the QoL of patients or further explore the antibiosis, anti-inflammation and antioxidation of NAC for NCFB.

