#### Inclusion criteria

(1) 18 years or older at enrolment; (2) having diagnosed with non-cystic fibrosis bronchiectasis (NCFB) by high-resolution computed tomography (HRCT) scans; (3) a forced expiratory volume in 1 s (FEV1) ≥ 30% of its predicted value in pulmonary function tests; (4) having had at least two pulmonary exacerbations requiring oral antibiotics or at least one pulmonary exacerbation necessitating intravenous antibiotics in the year before enrolment; and (5) having been in a stable state of NCFB for at least 4 weeks prior to randomisation.

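### The 90% power for exacerbations rests on an SD of 1 with no stated control rate and is likely optimistic; separately, 79:40 is a rounding slip worth about one point of power or less

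*Protocol article*

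**What the plan says.** The Sample size section sizes the two primary endpoints separately, at 2:1 allocation.

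- **SGRQ.** It takes a "mean difference (MD) of 6 points of SGRQ score as the smallest clinically important difference", an SD of 8.5, two-sided 5% significance and 90% power. This gives 64 and 32 evaluable patients. It continues: "assuming 20% of patients in each group may drop out or lose data integrity, we need to recruit 79 in the intervention group", with 40 controls.
- **Exacerbations.** "we regard MD of 0.7 times of exacerbation per year as the smallest clinically important difference between two group with a SD of 1", attributed to the earlier NAC trial in bronchiectasis. With the same 20% loss, "we also need to recruit 79 patients in NAC group and 40 patients in placebo group" ("α = 0.05, 1 - β = 0.9"). No evaluable number and no control-arm rate is given.

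Two other places bear on the rate. The Background says that "50% of patients with NCFB have two or more exacerbations annually". The Inclusion criteria require, in the year before enrolment, "at least two pulmonary exacerbations requiring oral antibiotics" or one event treated intravenously. The Statistical analysis section plans a Student's t test or a Wilcoxon rank-sum test for the primary outcomes.

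**The concern.** The main question is the SD of 1. A yearly exacerbation count normally has a variance at least as large as its mean, so a fixed SD carries a hidden assumption about the event rate. The protocol does not state that rate, and its own description of the population suggests one at which an SD of 1 is too low. Exacerbation count is one of two primary endpoints. If its real power is 70–80% rather than 90%, the chance of missing a true difference of 0.7 is two to three times the stated 10%, and a non-significant result would be easy to misread.

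The lesser question is whether 79:40 follows from the stated inputs, since it is claimed for both endpoints although their standardised differences are not identical.

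**Working it through.** **1. Reproducing the plan's figures.** For 2:1 allocation the control-arm size is n = 1.5 × (1.960 + 1.2816)² × (SD/MD)², where the squared sum is 10.507.

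- SGRQ: 1.5 × 10.507 × (8.5/6)² = 31.63 control and 63.26 NAC, rounded up to 32 and 64 as stated. The unrounded values divided by 0.8 are 39.5 and 79.1, so 79:40 evidently comes from inflating before rounding. From the stated 64, the figure is 64/0.8 = 80; 79 × 0.8 = 63.2.
- Exacerbations (two-sided test assumed, as for SGRQ): 1.5 × 10.507 × (1/0.7)² = 32.17 and 64.33. Divided by 0.8 these are 40.2 and 80.4, both above 40 and 79. Rounding first gives 65:33, hence 82:42, or in whole 2:1 sets 66:33, hence 83:42. No route gives 79:40.

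**2. What that costs.** 79:40 less 20% leaves about 63:32. Noncentral t power on the protocol's inputs is 89.6% for SGRQ (89.7% at 64:32) and 89.1% for exacerbations (90.2% at 66:33). The loss is about one point or less.

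**3. What an SD of 1 implies for a count.** If counts are Poisson and half the patients have two or more, then 1 − e^(−m)(1 + m) = 0.5, so m = 1.68 and SD = √1.68 = 1.30. That is for NCFB patients in general; entry to this trial also requires recent exacerbations.

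Under the alternative the NAC arm has a rate 0.7 lower and so a smaller variance. At 63:32 with Poisson variances, SE = √[(μ − 0.7)/63 + μ/32] and power ≈ Φ(0.7/SE − 1.96):

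- μ = 1.2: SE = √(0.5/63 + 1.2/32) = 0.213; power 90.7%
- μ = 1.5: SE = √(0.8/63 + 1.5/32) = 0.244; power 81.8%
- μ = 2.0: SE = √(1.3/63 + 2.0/32) = 0.288; power 68.0%

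**4. Power of the tests the protocol names.** The formula in step 3 allows unequal variances. Student's t pools them and does somewhat better here, because the larger variance sits in the smaller arm. Simulated power at 63:32, true difference 0.7, two-sided 5% (approximate; a repeat with 20,000 trials per cell agreed within one point):

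| Assumed control rate per year | Poisson: Student's t | Poisson: Wilcoxon | Dispersion 0.2: Student's t | Dispersion 0.2: Wilcoxon |
|---|---|---|---|---|
| 1.5 | 87% | 83% | 79% | 72% |
| 1.68 | 81% | 77% | 71% | 65% |
| 2.0 | 72% | 68% | 61% | 54% |

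Dispersion k means variance = μ + kμ². As a harsher case, k = 0.5 in the step 3 formula gives SE = √(1.12/63 + 2.625/32) = 0.316 and 60% at rate 1.5, and SE = √(2.145/63 + 4/32) = 0.399 and 42% at rate 2.0.

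The stated 90% therefore holds up to a control rate of roughly 1.2 to 1.4 a year, depending on the test, with little overdispersion. At those rates a drop of 0.7 is a reduction of 58% (0.7/1.2) to 50% (0.7/1.4).

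**The case against.** The strongest reply is that the SD is not invented: the protocol takes it from an earlier trial of the same drug in bronchiectasis, and that trial's figures are not available here. The on-study rate may also fall below the entry history through regression to the mean, and a patient can enter on a single intravenously treated event. The value of 1.68 assumes Poisson counts and starts from a statement about NCFB patients in general. All of this stands, and it is why the SD can be called likely optimistic but not wrong. One point pulls the other way: the on-study definition in the Primary endpoints section is symptom-based and does not require antibiotics, so it is broader than the entry criterion.

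Three stronger readings are tempting and are not supported.

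- A reader might infer from 64/0.8 = 80 or from 83:42 that the target fails to deliver 90%. On the protocol's inputs it delivers 89–90%. The noncentral t standard that leads to 66:33 for exacerbations would also reject 64:32 for SGRQ (89.7%), so 83:42 is no ground for enlarging the trial. Nor is 79:40 a fault because it is not a whole number of 2:1 blocks: no block size is given and a last block may be incomplete.
- A reader might infer that an SD of 1 requires a mean of at most 1. That is true within one arm, but the design SD is common to both arms, and two-thirds of patients have the lower rate under the alternative. The simple pooled Poisson SD at a control rate of 1.5 is √[(2 × 0.8 + 1.5)/3] = 1.02. An SD of 1 fits control rates of about 1.2 to 1.5.
- A reader might take the unequal-variance figures as the design's power. They are lower than Student's t by several points, up to about nine with overdispersion.

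**Conclusion.** The point holds in two parts of unequal weight. The minor part is certain: 79 does not follow from 64 with 20% loss, and 79:40 does not reproduce from the exacerbation inputs, at a cost of about one point of power or less. The main part is conditional: the 90% for exacerbations depends on an unstated control rate of no more than about 1.2 to 1.4 a year with little overdispersion, whereas the protocol's own text points to about 1.7 or more. At assumed rates of 1.68 to 2.0, power with the planned tests is about 68–81% for Poisson counts and 54–71% with dispersion 0.2.

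This rests on a true difference of 0.7, 63:32 evaluable patients, variance at least equal to the mean, and an assumed on-study rate that the document neither gives nor excludes.

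**What to change.** In the Sample size section:

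1. Correct the target to 80:40 = 120, or keep 119 and state that it gives about 89–90% power on the protocol's inputs. Remove the claim that the exacerbation inputs independently lead to 79:40.
2. State the control-arm exacerbation rate assumed and how the SD of 1 relates to it and to the cited trial.
3. Replace the flat 90% for exacerbations with the power of the planned test at the actual size, over control rates 1.0–2.0 and dispersion 0–0.5.

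The cost is one patient at most, some rewording, and a less favourable stated power for the second primary endpoint. No further enrolment or change of design is needed.
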